**FIGURE 1 bco270191-fig-0001:**
[figure not shown]
Visual from the DIPLANN website (IBiTech‐BioMMedA, Ghent University, Ghent, Belgium). Arteries in red, veins in blue, parenchyma in grey, cysts in purple, tumour in orange, ureter and pyelocaliceal system in yellow, perfusion zone in green. The 3D perfusion zone model can be rotated, and structures can be toggled on/off, and put on transparent. Arteries can be explored to see which artery perfuses which zone of the kidney. The percentage of estimated clamped parenchyma and clamped tumour can be noted in the top right. The surgeon can use this information to plan his surgical strategy. The model can be visualized on an adjacent PC, smartphone or tablet or can be visualized through the TilePro screen of the DaVinci surgical robot (Intuitive Surgical, Sunnyvale, CA, USA).

3D models will be created from CT images using the 3D modelling platform from an external, commercial company (MEDANNOT s.r.o., Spania Dolina, Slovakia). On this platform, an automated AI‐generated first segmentation is made (using our own previous 3D data^3^). Afterwards, this segmentation is further handled by the study team and an experienced uroradiologist to ensure correct segmentation and add final detail. Afterwards, on this 3D model, a perfusion zone algorithm is used, developed by Ghent University (research group IBiTech – BioMMedA, Department of Electronics and Information Systems, Faculty of Engineering and Architecture).

### Study procedures

5.2

An overview of the study flow is presented in Table 3 and Figure 2.

**TABLE 3 bco270191-tbl-0003:** Overview of all study‐specific procedures, following SPIRIT guidelines.^4^

TIMEPOINT	STUDY PERIOD											
	Enrolment		Allocation	Post‐allocation								Close‐out
	Screening (visit)	Technical	Randomization	Pre‐op (visit)	Day before operation (or earlier after pre‐op visit)	Day of operation	Post‐op day 1	Discharge *	1 m (visit) **	3 m (visit) ***	6 m (visit) ***	12 m (visit) ***
**ENROLMENT:**												
**Eligibility screen**	x											
**Informed consent**	x											
**Sending CT images to Central Imaging Analysis Centre for design of 3D models and perfusion models (including validation by uro‐radiologist)**		x										
**Possibility of selective clamping assessed by independent surgeon**		x										
**Allocation**			x									
**INTERVENTIONS:**												
** *3D perfusion model + CT available for patient counselling, preoperative planning and perioperative guidance* **			x									
** *Only CT available* **			x									
**ASSESSMENTS:**												
**Preoperative study visit explaining the procedure using either CT scan or 3D model**				x								
**Physical examination including height, weight, abdominal examination**				x								
**Blood examination including Hb, creatinine, eGFR**				x			x					
**Blood examination including creatinine, eGFR**								x	x	x	x	x
**Patient questionnaire regarding knowledge**				x								
**Hospital Anxiety and Depression Scale (HADS) + Symptom Distress Thermometer (SDT)**				x								
**EORTC QLQ‐C30 questionnaire**				x						x	x	x
**Online assessment by surgeon regarding selective arterial clamping information**					x							
**RAPN surgical procedure**						x						
**Postoperative questionnaire for the surgeon with surgical details and information on arterial clamping**						x						
**Histopathological examination of renal tumour**						x						
**Follow‐up consultations and monitoring of complications**									x	x	x	x

* Last measurement before discharge.

** Time window of 2 weeks before and 2 weeks after.

*** Time window of 4 weeks before and 4 weeks after.

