**Secondary Endpoints**
*Key Secondary Endpoints*
Change in eGFR at 6 months after surgery compared to eGFR preoperatively
Clamping strategy performed (SC or MAC)
*Secondary Endpoints*
Time to dissect hilum (minutes) as analysed on postoperative surgical video analysis
Conversion from SC to MAC
*Safety Endpoints*
Intra‐operative and 90‐day postoperative complications
Estimated blood loss during surgery (mL)
Concordance between the 3D perfusion model and peroperative kidney surface perfusion as visualized by indocyanine green (ICG) as estimated by postoperative surgical video analysis
*Exploratory Endpoints*
Patients' health
eGFR (CKD‐EPI) < 45 ml/min at 6 months after surgery
Change in eGFR (CKD‐EPI) after surgery at other time points up to 1 year (POD1, last measurement before discharge, postoperatively 1 month, 3 months, 12 months) compared to eGFR preoperatively
Ischemia time during surgery (seconds)
Positive surgical margin (PSM)
Robotic console time of surgery (minutes)
Length of hospital stay after surgery (days)
2 Patients’ insight
Quality of life (according to EORTC QLQ‐C30) up until 1 year after surgery (preoperatively, 3 months, 6 months, 12 months
Preoperative anxiety for surgery questionnaire (Hospital Anxiety and Depression Scale (HADS) + Symptom Distress Thermometer (SDT))
Preoperative patient knowledge questionnaire
3 Surgeon's decision
Time to dissect kidney (minutes)
Superselective clamping (yes/no)
% parenchyma rendered ischemic
Conversion from PN to RN
Time to prepare for surgery (minutes)

* For the primary objective, SC needs to be deemed possible either according to the DIPLANN‐tool in combination with conventional CT imaging or according to conventional CT imaging only, as assessed by an independent surgeon (between inclusion and randomization) who will not be involved in the RAPN surgical procedure, in order to be included in the analysis set. On the DIPLANN tool, SC is deemed feasible if ≥ 90% tumour ischemia and ≤ 70% renal parenchyma ischemia can be achieved. If these criteria are met, but it is technically or anatomically not feasible according to the independent surgeon to perform SC, he can deviate from these criteria and thus claim SC is not deemed possible. As a secondary objective, this endpoint will be analysed in the total study population.

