**FIGURE 2 bco270191-fig-0002:**
[figure not shown]
Schematic presentation of the PODRACING workflow.

After checking eligibility, informed consent is signed, and anonymized CT images are sent to a central imaging analysis team for design of the 3D models (using the MEDANNOT 3D segmenting platform) and perfusion zone models (using the DIPLANN tool by IBiTech‐BioMMedA, Ghent University). The 3D models and the perfusion zone models will be manufactured centrally, under the supervision of an expert uroradiologist. A central independent surgeon will assess if SC is deemed possible on CT and/or the DIPLANN tool (for the primary objective and for stratification), first on CT only, afterwards on the DIPLANN tool. On the DIPLANN tool, SC is deemed feasible by the independent surgeon if ≥ 90% tumour ischemia and ≤ 70% renal parenchyma ischemia can be achieved. If these criteria are met, but it is technically or anatomically not feasible according to the independent surgeon to perform SC, he can deviate from these criteria and thus claim SC is not deemed possible. These feasibility thresholds were selected based on expert consensus and prior technical implementation of the perfusion zone models and represent a pragmatic balance between achieving near‐complete tumour ischemia for oncological safety and limiting ischemic exposure of healthy renal parenchyma. After this, randomization will take place and the local team of the respective study site will be notified to which group the patient is assigned. If randomized in the study group, the 3D perfusion zone model will be accessible on the DIPLANN website for the treating surgeon at the local study site. The surgeon can now explain the procedure to the patient using the 3D model. If the patient is randomized in the control group, there will be no 3D model available on the DIPLANN website for the surgeon, and he/she continues only with the CT scans.

Apart from the availability of a 3D perfusion zone model, study procedures are identical for the study group and control group.

Next to explaining the procedure with or without the study model, a preoperative visit consists of checking for preoperative kidney function and haemoglobin, an abdominal examination and completing quality of life, knowledge and anxiety questionnaires.

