#### Other analyses

5.9.9

Endpoints that are measured repeatedly will be analysed using generalized linear mixed models with a random intercept for patient, including time, arm, a two‐way interaction between time and arm and the stratification factors: whether SC is deemed possible, hospital, and the highest individual PADUA classification in the fixed effects part of the model.

Continuous endpoints measured at one point in time will be analysed using a linear regression model including arm and the stratification factors: whether SC is deemed possible, hospital and the highest individual PADUA classification. Log‐normally distributed endpoints will be log‐transformed before analysis.

Binary endpoints measured at one point in time will be analysed using a binary logistic regression model (with logit link function), including arm and the stratification factors: whether SC is deemed possible, hospital and the highest individual PADUA classification.

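### No quality-of-life or anxiety score is collected before allocation, so the preoperative QLQ-C30 is a post-allocation outcome and cannot serve as a clean baseline

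*Protocol article*

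**What the plan says.** Table 3 (section 5.2) orders its columns as screening, technical, randomization and then the pre-op visit, which stands under the post-allocation heading. The text agrees. Once the independent surgeon has judged whether selective clamping is possible, "After this, randomization will take place and the local team of the respective study site will be notified to which group the patient is assigned". The study is described as unblinded (section 2).

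The pre-op visit carries the row "Preoperative study visit explaining the procedure using either CT scan or 3D model". Table 3 lists the experimental intervention as "3D perfusion model + CT available for patient counselling, preoperative planning and perioperative guidance", so counselling is part of what is randomized. Section 5.2 adds that the same visit includes "completing quality of life, knowledge and anxiety questionnaires". It does not give the order of explanation and questionnaires. The screening column contains only the eligibility check and consent.

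Table 1 files these measures under the exploratory heading of patients' insight. The QLQ-C30 entry reads "Quality of life (according to EORTC QLQ‐C30) up until 1 year after surgery (preoperatively, 3 months, 6 months, 12 months". Anxiety (HADS plus distress thermometer) and knowledge are single preoperative measurements. Section 5.9.9 analyses repeated endpoints with a mixed model "including time, arm, a two‐way interaction between time and arm and the stratification factors". Endpoints measured once are regressed on arm and the stratification factors.

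**The concern.** Two kinds of measurement share one post-allocation visit. Anxiety and knowledge are outcomes of the counselling and belong after it. The preoperative QLQ-C30 is the first point of a course that runs to 12 months, and a reader will naturally take it as the starting value. By then the patient may know the allocation and may have been counselled with the 3D model.

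Widening patients' insight is one of the three limbs of the trial's hypothesis (section 1), so the investigators themselves expect the tool to act on patients through this visit. If it does, the first QLQ-C30 may already carry part of the effect, and a contrast that subtracts that score removes the effect again. No later analysis plan can supply a pre-allocation score that was never collected.

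**Working it through.** There is no figure in the plan to reproduce on this point. The check is a short derivation, a small simulation and a standard-error calculation.

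**Inputs.** From the documents: 235 patients, 1:1 allocation; QLQ-C30 preoperatively and at 3, 6 and 12 months; a random-intercept model with time, arm and time by arm. Assumed: d, the shift in the experimental arm at the pre-op visit from counselling or knowledge of the allocation; e, the effect at later visits; and the correlation r between a screening score and the preoperative score. All effects are in units of about one SD.

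**1. What each contrast estimates.**
- Arm difference at the pre-op visit: d
- Arm difference at a later visit: e
- Time-by-arm term (change from preoperative): e - d

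Read as the treatment effect, the third contrast is biased by (e - d) - e = -d. The second is unbiased whatever d is.

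**2. Simulation.** 235 patients, four time points, between-patient and residual SD each 0.7, the model above without stratification factors, 60 runs per scenario, contrasts at 6 months:

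| d | e | Time-by-arm term | Expected e - d | Arm difference at 6 months | Expected e |
|---|---|---|---|---|---|
| 0 | 0 | -0.02 | 0 | 0.01 | 0 |
| 0.2 | 0 | -0.21 | -0.2 | -0.01 | 0 |
| 0.2 | 0.2 | -0.01 | 0 | 0.19 | 0.2 |
| 0.4 | 0.2 | -0.21 | -0.2 | 0.22 | 0.2 |
| 0.2 | 0.4 | 0.20 | 0.2 | 0.38 | 0.4 |

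The variance of one score is 0.49 + 0.49 = 0.98, and the variance of a change is 2 × 0.49 = 0.98. Each contrast therefore has a standard error of about sqrt(4 × 0.98/235) = 0.129 per run, or 0.129/sqrt(60) = 0.017 for the mean of 60 runs. The departures from expectation are of that order.

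In the second row, a counselling effect that fades looks like a harm on the change scale. In the third, a constant benefit of 0.2 SD gives a time-by-arm term of about zero, yet it is plain in the arm difference at the visit.

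**3. Anxiety without a pre-allocation score.** The standard error of the arm difference is 2/sqrt(235) = 0.130 SD. Adjusting for a screening score multiplies it by sqrt(1 - r²):
- r = 0.5: 0.130 × 0.866 = 0.113 SD
- r = 0.6: 0.130 × 0.800 = 0.104 SD
- r = 0.7: 0.130 × 0.714 = 0.093 SD

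This is a gain in precision only; no bias is being removed.

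**The case against.** The strongest reply is that the article never defines a change in quality of life. It lists the QLQ-C30 as a score on four occasions, the preoperative one among them. Where the authors mean change, they write it: "Change in eGFR at 6 months after surgery compared to eGFR preoperatively". The planned model gives a between-arm difference at every visit, and which contrast will be reported may be settled in a full protocol or analysis plan that is not shown. All of this stands, and it limits the point to change or time-by-arm readings.

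A second reply is that contamination has not been shown. The order within the visit is not given, and a QLQ-C30 completed before the explanation would escape the counselling effect. This also stands. It leaves the influence of knowing the allocation in an unblinded trial, and the absence of any earlier score by which to check.

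Third, a reader might infer that the anxiety comparison is unsound because it has no baseline. The documents do not support that. Anxiety is intended as a preoperative outcome, the arms are randomized, and the standard error already reflects chance imbalance.

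What the replies do not answer is that Table 3 is the full schedule of study procedures and contains no questionnaire before allocation.

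**Conclusion.** The point holds in a limited form. The preoperative QLQ-C30 is a post-allocation outcome. A change-from-preoperative or time-by-arm reading is biased by -d if counselling or knowledge of the allocation shifts that score by d. The size of d is unknown and may be zero; 0.2 and 0.4 SD above are illustrations. Between-arm differences at each visit are unbiased.

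Two stronger readings should be resisted. One is that the baseline is contaminated: that is possible but not established. The other is that a lasting benefit would vanish from the analysis: it would vanish from one contrast only, and the article does not name that contrast as its quality-of-life estimate.

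For anxiety, the loss is precision alone. The standard error would be 13%, 20% or 29% smaller (1 - 0.866, 1 - 0.800, 1 - 0.714) at the three assumed correlations. The endpoints are exploratory (Table 1, section 5.9.11), so the priority is low and the primary and key secondary results are unaffected.

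**What to change.** - **Schedule (Table 3).** Collect the baseline QLQ-C30 and one HADS plus distress thermometer at the screening visit, after consent and before allocation. Keep HADS, distress thermometer and the knowledge questionnaire at the pre-op visit, and state that they are completed after the explanation.
- **Analysis (section 5.9.9).** Use the screening scores as baseline covariates.
- **Patients already enrolled under the present schedule.** Treat the preoperative QLQ-C30 as an outcome and report the difference between arms at each visit, not change from the preoperative value.

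The cost is a schedule amendment and a few minutes of questionnaires at an existing visit. No visit is added. Patients already randomized will remain without a pre-allocation score, so the gain is larger the earlier in recruitment the change is made.

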**FIGURE 2 bco270191-fig-0002:**
[figure not shown]
Schematic presentation of the PODRACING workflow.

After checking eligibility, informed consent is signed, and anonymized CT images are sent to a central imaging analysis team for design of the 3D models (using the MEDANNOT 3D segmenting platform) and perfusion zone models (using the DIPLANN tool by IBiTech‐BioMMedA, Ghent University). The 3D models and the perfusion zone models will be manufactured centrally, under the supervision of an expert uroradiologist. A central independent surgeon will assess if SC is deemed possible on CT and/or the DIPLANN tool (for the primary objective and for stratification), first on CT only, afterwards on the DIPLANN tool. On the DIPLANN tool, SC is deemed feasible by the independent surgeon if ≥ 90% tumour ischemia and ≤ 70% renal parenchyma ischemia can be achieved. If these criteria are met, but it is technically or anatomically not feasible according to the independent surgeon to perform SC, he can deviate from these criteria and thus claim SC is not deemed possible. These feasibility thresholds were selected based on expert consensus and prior technical implementation of the perfusion zone models and represent a pragmatic balance between achieving near‐complete tumour ischemia for oncological safety and limiting ischemic exposure of healthy renal parenchyma. After this, randomization will take place and the local team of the respective study site will be notified to which group the patient is assigned. If randomized in the study group, the 3D perfusion zone model will be accessible on the DIPLANN website for the treating surgeon at the local study site. The surgeon can now explain the procedure to the patient using the 3D model. If the patient is randomized in the control group, there will be no 3D model available on the DIPLANN website for the surgeon, and he/she continues only with the CT scans.

Apart from the availability of a 3D perfusion zone model, study procedures are identical for the study group and control group.

Next to explaining the procedure with or without the study model, a preoperative visit consists of checking for preoperative kidney function and haemoglobin, an abdominal examination and completing quality of life, knowledge and anxiety questionnaires.

For the primary endpoint, the surgeon needs to lock his/her final clamping strategy on the DIPLANN website (with or without the use of a 3D model) and time his/her planning process with a built‐in timer system. After locking in the clamping strategy, he/she can now proceed with the RAPN procedure (with or without the peri‐operative use of a 3D model). The surgeon can use his/her preferred operating method for RAPN (no limitations in surgical approach or robotic system). Important during the surgery is the use of indocyanine green (ICG) after clamping the artery (for a secondary validation endpoint) and recording the surgery, to objectively note surgery details (e.g. hilar dissection time). Postoperative hospitalization course is fully decided by the surgeon. Blood examination results of the first postoperative day and last before discharge are collected.

Postoperative visits entail visits at 1 month, 3 months, 6 months and 12 months for adverse event monitoring, kidney function follow‐up and/or follow‐up quality of life questionnaires. Postoperative imaging happens outside of the study and at the treating physician's pace of choice (usually according to current EAU guidelines for RCC follow‐up.^1^

### Sample size determination

5.3

The study is powered for its primary objective, which targets patients in whom SC is deemed possible either according to the DIPLANN‐tool in combination with conventional CT imaging or according to conventional CT imaging only, as assessed by an independent surgeon between inclusion and randomization.

A sample size of 196 patients in whom SC is deemed possible is needed to achieve at least 80% power to detect an absolute risk difference of 15.6% in favourable outcome (planning and performing as planned a SC strategy) between the DIPLANN‐tool in combination with conventional CT imaging and conventional CT imaging alone, using an exact binomial test at the two‐sided 5% significance level when the design is balanced (1:1 allocation ratio) and the true rate of favourable outcome is 73.4% with conventional CT imaging alone and 89.0% with the DIPLANN‐tool in combination with conventional CT imaging.

The sample size was increased to 198 patients to allow for a 1% drop‐out. The sample size was further increased to 202 patients in whom SC is deemed possible (101 in each group), to foresee an interim analysis for efficacy when 50% of the primary endpoints are measured, using a group sequential design with O'Brien Fleming alpha spending function.

When SC is deemed possible in 86% of patients, the total sample size of patients diagnosed with localized kidney cancer who are planned to undergo renal cancer surgery will be 235. The assumed rate of SC performed as predicted, with a standard of care of 73.4%, is based on other studies.^6^, ^7^

Recruitment will continue until 202 patients in whom SC is deemed possible are randomized.

### Methods of data collection

5.4

Data collection will comply with GDPR (EU 2016/679). Source data will be recorded at the subject's visit, with protocol‐required data entered into eCRFs in REDCap, a secure web‐based system licensed to HIRUZ.

Authorized study staff will enter and correct data in accordance with ISO 14155. eCRFs will be signed and verified for accuracy and completeness by the principal investigator or a co‐investigator, and reviewed by trained monitors. Data cleaning will be performed by the sponsor. Patient questionnaires will be entered directly as source data, and essential documents will be retained for at least 10 years in line with regulatory requirements.

### Recruitment and consent

5.5

Recruitment will take place at the urology departments of the different participating hospitals by a participating clinical investigator. This can only take place after radiographic confirmation of a renal lesion on a multiphase CT scan.

Prior to entry in the study, the investigator will explain to potential subjects the study and the implications of participation. Subjects will be informed that their participation is voluntary and that they may withdraw consent to participate at any time. Participating subjects will be told that their records may be accessed by competent authorities and by authorized persons without violating the confidentiality of the subject, to the extent permitted by the applicable law(s) and/or regulations. By signing the Informed Consent Form (ICF), the subjects are authorizing such access.

